#### Concealment mechanism {16b}

Generated allocation sequence is to be concealed in opaque, sealed envelopes that are consecutively numbered. An independent research assistant is responsible for keeping these envelopes unopened and allocated.

#### Implementation {16c}

The allocation sequence will be generated by a statistician. Participants who are eligible for this trial and willing to give written consent will be enrolled by a trial researcher. The research assistant will directly inform the clinician about the group allocation.

### Assignment of interventions: blinding

#### Who will be blinded {17a}

Due to logistic reasons, it will not be feasible to blind the natural course of this study to patients nor clinicians. However, all endpoints will be adjudicated by an independent imaging core lab or the clinical event committee, who are blinded to the group allocation.

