**Fig. 1 Fig1:**
[figure not shown]
Flowchart of the study design

**Table 1 Tab1:** Schedule of enrollment, interventions, and examinations

Time point	Study period						
	Enrolment	Allocation	Post-allocation				
	1 week pre	0	1 month	3 months	6 months	12 months	24 months
Enrollment							
Eligibility screen	X						
Informed consent	X						
Allocation		X					
Interventions							
Standard care			X	X	X	X	X
Standard care plus fosinopril			X	X	X	X	X
Assessments							
Demographics	X						
Physical examinations	X		X	X	X	X	X
Medical history	X		X	X	X	X	X
Laboratory tests	X		X	X	X	X	X
NYHA class	X		X	X	X	X	X
Transthoracic echocardiography	X		X	X	X	X	X
CMR		X					X
KCCQ		X	X	X	X	X	X
6-min walk test		X	X	X	X	X	X
Adverse events			X	X	X	X	X

*NYHA* New York Heart Association, *CMR* cardiac magnetic resonance, *KCCQ* Kansas City Cardiomyopathy Questionnaire

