### Data collection and management

#### Plans for assessment and collection of outcomes {18a}

Severe AS patients who underwent TAVI will be approached and consented for screening for eligibility. Screening evaluations include brief physical examinations, blood laboratory tests, and reviewing of medical history. Heart failure-related symptoms will be assessed for an NYHA functional classification. Transthoracic echocardiography will be conducted to assess cardiac function.

The following information will be collected during baseline evaluations: (1) demographics including date of birth, gender; (2) physical examinations including body weight, body height, resting pulse, and blood pressure; (3) any major previous health problems and use of medication by reviewing health records; (4) NYHA function capacity class by examining related symptoms; (5) results of laboratory tests including full blood count, blood lipids, glucose, liver function, renal function, and NT-ProBNP; (6) KCCQ score and results of 6MWT. Follow-up visits will take place 30 days, 3 months, 6 months, 12 months, and 24 months from randomization. At each follow-up visit, patients will be asked for any specific symptoms, any changes in the use of medication, and any adverse events. A brief physical examination will be performed to measure the resting pulse and blood pressure. Blood samples will be taken for the laboratory tests including NT-ProBNP. Transthoracic echocardiography will be performed to evaluate LV function. Moreover, NYHA function capacity class, KCCQ, and 6MWT will be evaluated. CMR scanning will be performed at baseline and be repeated at the 24-month follow-up visit to assess LV volume, mass, and function. CMR images will be analyzed independently by a central imaging core lab (West China Hospital Radiology Medicine lab). All endpoints will be adjudicated by an independent clinical events committee blinded for group allocation.

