#### Kansas City cardiomyopathy questionnaire

KCCQ is used to assess patients’ quality of life [14]. The KCCQ is self-administered, but patients can also complete the questionnaire by interview through a clinician. On average, it will take 4 to 6 min to complete the KCCQ.

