#### Transthoracic echocardiography protocol

Transthoracic echocardiography will be performed using commercially available ultrasound systems at each participating sites. In order to maintain consistency, all measurements will be performed according to the expert consensus on adult transthoracic echocardiography reporting [15].

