## Oversight and monitoring

### Composition of the coordinating center and trial steering committee {5d}

The coordinating center is the West China Hospital. The trial steering committee consists of principal investigators at each study site responsible for interventions (standard care for the control group, standard care plus fosinopril for the intervention group). Other clinicians of the local Heart Team will be responsible for follow-up, data collection, and logistic support for the trial. The endpoint adjudication committee consists of an imaging core lab and two cardiologists.

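### The protocol says every endpoint is adjudicated blind, but NYHA class, KCCQ and 6MWT are produced by patients and site clinicians who know the arm

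*Protocol article*

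**What the plan says.** Who will be blinded {17a} concedes that "it will not be feasible to blind the natural course of this study to patients nor clinicians", and then claims that "all endpoints will be adjudicated by an independent imaging core lab or the clinical event committee, who are blinded to the group allocation". Plans for assessment and collection of outcomes {18a} repeats the claim with a single body: "All endpoints will be adjudicated by an independent clinical events committee blinded for group allocation".

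Other sections describe how the endpoints are obtained:

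- Outcomes {12} lists NYHA class, KCCQ and 6MWT as secondary outcomes twice: as 24-month values (item 6) and as changes (item 7). Item 1 is change in LVEF, with no modality named.
- Implementation {16c}: "The research assistant will directly inform the clinician about the group allocation".
- Composition of the coordinating center {5d}: "Other clinicians of the local Heart Team will be responsible for follow-up, data collection, and logistic support for the trial".
- Kansas City cardiomyopathy questionnaire: "The KCCQ is self-administered, but patients can also complete the questionnaire by interview through a clinician".
- Six-minute walk test: the test is run at each site, with a common manual and scripted encouragement.
- Transthoracic echocardiography protocol: "Transthoracic echocardiography will be performed using commercially available ultrasound systems at each participating sites". No central reading is described there. Central reading by the core lab is described in {18a} for CMR only.
- Table 1 under Participant timeline {13} marks baseline NYHA, laboratory tests and echocardiography in the column one week before allocation. It marks CMR, KCCQ and 6MWT in the time-0 column, headed allocation.

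**The concern.** Blinded adjudication protects an endpoint when the assessor can form an independent judgement from material that does not carry the allocation, such as an image or an event dossier. A questionnaire answer, a symptom grade and a walking distance are already complete when they leave the visit. If the patient or the clinician knew the arm, any expectation effect is in the recorded value, and a committee has nothing further to judge.

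The control group receives standard care with no placebo, so such an effect could favour fosinopril on all three measures. Entry also requires NYHA class I, so change in NYHA class can only record deterioration, and it is graded by staff not stated to be blinded. Heart failure status and quality of life are named secondary objectives. A reader who takes the blinding sentence at face value would credit these results with protection that they lack.

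Two further points bear on the same claim. If LVEF could come from site echocardiography or from core-lab CMR, whether that endpoint is read blind depends on a choice that the article does not fix. If baseline KCCQ or 6MWT is recorded after the arm is known, the baseline itself can be influenced, and the change scores in item 7 inherit that.

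**Working it through.** No figure in the plan measures this point, so the check is a comparison of sections followed by a count.

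**Step 1. Endpoint by endpoint.**

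| Endpoint | How it is obtained | Does blinded adjudication hold? |
|---|---|---|
| LV mass index (primary) | CMR, read by the core lab ({18a}, CMR protocol) | Yes, as stated in {17a} |
| All-cause death, cardiac death, heart failure re-admission | Clinical events | Yes, a blinded committee can adjudicate these |
| NT-ProBNP | Laboratory value | None described; not a matter of judgement |
| LVEF | Modality not named | Yes if CMR; reader not stated if echocardiography |
| NYHA class | Graded from symptoms at the visit | No |
| KCCQ | Patient answers, or clinician interview | No |
| 6MWT | Effort-dependent test run at the site | No |

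The last three rows follow from {17a} (patients and clinicians not blinded), {16c} (the clinician is told the arm) and {5d} (local Heart Team clinicians collect follow-up data). No section names a blinded assessor for them or says how they would be adjudicated.

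**Step 2. How many secondary endpoints this covers.** There are seven numbered items. There are eight distinct measures: LVEF, all-cause death, cardiac death, heart failure re-admission, NT-ProBNP, NYHA, KCCQ and 6MWT. Counting the 24-month value and the change separately gives 5 + 3 × 2 = 11 listed comparisons.

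| Count | NYHA, KCCQ, 6MWT | Adding LVEF, if it were read at site |
|---|---|---|
| Numbered items | 2/7 = 29% | 3/7 = 43% |
| Distinct measures | 3/8 = 38% | 4/8 = 50% |
| Listed comparisons | 6/11 = 55% | 7/11 = 64% |

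**Step 3. LVEF.** The inclusion criteria measure LVEF by echocardiography, and the introduction names both CMR and echocardiography for evaluating remodeling. {18a} has CMR measuring LV function at baseline and 24 months, and echocardiography evaluating it at every follow-up visit. Item 1 of the secondary outcomes can therefore be read either way.

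**Step 4. Baseline timing.** {18a} lists KCCQ and 6MWT among the baseline evaluations and places CMR at baseline. Table 1 puts all three at time 0 together with allocation. Neither gives an order within that time point.

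**Step 5. The adjudicating body.** {17a} gives endpoints to the core lab or the event committee, {18a} gives all of them to the event committee, and {5d} describes one adjudication committee made up of the core lab and two cardiologists.

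**Step 6. Effect on the design figure.** The plan's power statement concerns the primary endpoint only and is untouched. With 10% dropout, 100 × 0.9 = 90 per group. The standard error is 35 × √(2/90) = 5.22; 20/5.22 − 1.96 = 1.87; power ≈ 96.9%, consistent with the stated figure of more than 90%.

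**The case against.** The strongest reply is that the trial calls itself open-label throughout, so no careful reader will think that a self-completed questionnaire was blinded. The endpoint that carries the conclusion is read by a core lab described as blinded. The walk test has a standard manual and scripted phrasing, and those who collect follow-up data are listed separately from the site investigators responsible for the interventions.

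Much of this is correct, and it limits the point to secondary outcomes. It does not rescue the sentence. Scripted phrasing reduces variation between testers but blinds neither tester nor patient. The separate follow-up clinicians are nowhere said to be unaware of the arm, and {17a} says that clinicians are not blinded. Stating in two sections that all endpoints are adjudicated blind is a positive claim that the same document contradicts.

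A second reply is that the choice of modality for LVEF, and the order of procedures on the allocation day, are details that a full protocol or analysis plan may settle. As omissions alone, that would be fair. LVEF matters here because the blinding claim covers it and only one of its two possible sources is shown to be read centrally. The timing matters because Table 1 itself puts these assessments in the allocation column of an open-label trial.

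Three stronger readings are tempting, and the document does not support them:

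- That most secondary endpoints lack blinding. A majority appears only when each instrument is counted twice (6 of 11). It is 2 of 7 by item and 3 of 8 by measure, and even adding LVEF gives no more than half.
- That LVEF will be read at the sites. Echocardiography is performed there, but so is CMR, which is read centrally. Where a scan is acquired does not show who reads it.
- That baseline is measured after the arm is known. The time-0 column permits that order but does not show it, and the intervention rows begin at 1 month.

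**Conclusion.** The claim of blinded adjudication for all endpoints is wrong for NYHA class, KCCQ and 6MWT, which supply secondary outcomes 6 and 7. It stands for LV mass index, deaths and heart failure re-admission. The conclusion does not depend on how the endpoints are counted, because one such measure is enough to contradict a statement about all of them.

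It rests on two readings: that the clinicians who are not blinded under {17a} include those collecting follow-up data under {5d}, and that no blinded assessor for these measures is named elsewhere. A blinded assessor could in principle be added for NYHA and 6MWT, but the patient would still know the arm. The direction of bias favouring fosinopril is plausible, but its size cannot be derived from the document.

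The LVEF and baseline-timing points are ambiguities, not demonstrated faults. They are worth closing because doing so costs almost nothing. The point merits a correction but does not threaten the primary analysis.

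**What to change.** 1. In {17a} and {18a}, limit the blinded-adjudication statement to CMR measures and clinical events (death, cardiac death, heart failure re-admission), and state that NYHA class, KCCQ and 6MWT are assessed open-label. Describe the adjudicating body in the same way in {17a}, {18a} and {5d}.
2. In Outcomes {12}, define secondary outcome 1 as change in LVEF by core-lab CMR from baseline to 24 months.
3. In Table 1 and {18a}, require baseline CMR, KCCQ and 6MWT to be completed before allocation is released.

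Labelling the three open-label measures as supportive, and preferring self-completion of the KCCQ to clinician interview, are optional.

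The cost is wording and the order of procedures already planned, with no extra scans and no change to sample size, power or alpha. There are two downsides: the patient-reported and functional outcomes carry a more modest claim, and the defined LVEF change is available only at 24 months, whereas echocardiography would give it at every visit.

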#### Procedure for unblinding if needed {17b}

Not applicable, the trial is an open-label design.

### Data collection and management

#### Plans for assessment and collection of outcomes {18a}

Severe AS patients who underwent TAVI will be approached and consented for screening for eligibility. Screening evaluations include brief physical examinations, blood laboratory tests, and reviewing of medical history. Heart failure-related symptoms will be assessed for an NYHA functional classification. Transthoracic echocardiography will be conducted to assess cardiac function.

The following information will be collected during baseline evaluations: (1) demographics including date of birth, gender; (2) physical examinations including body weight, body height, resting pulse, and blood pressure; (3) any major previous health problems and use of medication by reviewing health records; (4) NYHA function capacity class by examining related symptoms; (5) results of laboratory tests including full blood count, blood lipids, glucose, liver function, renal function, and NT-ProBNP; (6) KCCQ score and results of 6MWT. Follow-up visits will take place 30 days, 3 months, 6 months, 12 months, and 24 months from randomization. At each follow-up visit, patients will be asked for any specific symptoms, any changes in the use of medication, and any adverse events. A brief physical examination will be performed to measure the resting pulse and blood pressure. Blood samples will be taken for the laboratory tests including NT-ProBNP. Transthoracic echocardiography will be performed to evaluate LV function. Moreover, NYHA function capacity class, KCCQ, and 6MWT will be evaluated. CMR scanning will be performed at baseline and be repeated at the 24-month follow-up visit to assess LV volume, mass, and function. CMR images will be analyzed independently by a central imaging core lab (West China Hospital Radiology Medicine lab). All endpoints will be adjudicated by an independent clinical events committee blinded for group allocation.

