#### Exclusion criteria

Subjects presenting any of the following exclusion criteria will be excluded from the study: (1) concomitant with other significant valvular heart disease needs intervention; (2) contraindication or intolerance for the use of fosinopril including a history of angioneurotic edema, hypotension (defined as systolic blood pressure < 100 mmHg or diastolic blood pressure < 60 mmHg), estimated glomerular filtration rate < 30 mL/min/1.73 m^2^, and random serum potassium > 5.4 mmol/L; (3) life expectancy < 1 year; (4) contraindication to CMR, f.e., implantation of cardiac resynchronization therapy devices that are non-magnetic resonance conditional; and (5) prior history of myocardial infarction or dilated cardiomyopathy.

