#### Intervention description {11a}

Patients allocated in the intervention group will receive an additional use of fosinopril with an initial dose of 10 mg once daily. If the patient is well-tolerated, they will be titrated to a maximum dose of 40 mg once daily. Titration of fosinopril will be performed at the 1-month follow-up visit and afterward.

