### Composition of the data monitoring committee, its role, and reporting structure {21a}

The data and safety monitoring committee (DSMC) will consist of four qualified members from the West China Hospital, including at least one statistician and cardiology expert independent from the site trial staff. The DSMC is independent from the trial researchers, blinded to the assignment, and will monitor the progress of the trial and safety issues and require data for analyses.

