### Adverse event reporting and harms {22}

Adverse events reported by the participant or noticed by the clinician will be reported directly (maximum within a week) to the DSMC and recorded in the digital case reported form and data manage system.

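### The safety committee is blinded to assignment in an open-label trial, with no stated by-arm safety review and no route to unmask

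*Protocol article*

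**What the plan says.** **Safety committee.** The section on the data monitoring committee {21a} states: "The DSMC is independent from the trial researchers, blinded to the assignment, and will monitor the progress of the trial and safety issues". The same sentence adds that the committee can call for data to analyse. Adverse event reporting {22} says that events "will be reported directly (maximum within a week) to the DSMC".

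**Surrounding design.** Blinding {17a} says that neither patients nor clinicians are blinded, and that endpoints go to an imaging core lab or a clinical event committee, both blinded to allocation. The unblinding section {17b} is marked not applicable because the trial is open label. The interim analysis section {21b} is marked not applicable because none will be done.

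**Laboratory tests.** The exclusion criteria include "random serum potassium > 5.4 mmol/L". The outcome collection section {18a} describes screening as "Screening evaluations include brief physical examinations, blood laboratory tests, and reviewing of medical history". It lists for baseline "results of laboratory tests including full blood count, blood lipids, glucose, liver function, renal function, and NT-ProBNP", and for follow-up says "Blood samples will be taken for the laboratory tests including NT-ProBNP". Table 1 schedules laboratory tests at screening and at all five follow-up visits.

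**The concern.** The DSMC is the only body with a stated safety remit, and the article denies it knowledge of the arm. Everyone treating the patients has that knowledge. Blinding a committee can protect outcome assessment, but here the core lab and the event committee assess outcomes and are blinded separately. The DSMC's own blinding therefore protects little.

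At stake is whether an excess of harm in one arm can be recognised while patients are still being treated. Follow-up lasts 24 months and the intervention dose may rise during it ("Titration of fosinopril will be performed at the 1-month follow-up visit and afterward"). A committee that sees only overall event counts cannot tell a harmful arm from a uniformly moderate background rate. A committee that sees two unlabelled arms can see a difference, but must know its direction before it can advise.

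**Working it through.** **The plan's own figure.** The article gives no figure on safety monitoring. Its only design figure is power above 90% for a 20 g/m² difference, with SD 35 g/m², alpha 0.05, 100 per group and 10% dropout. With 90 evaluable per group, 20 / (35 × √(2/90)) = 3.83, and Φ(3.83 − 1.96) is about 96.9%. The statement is reproduced, and the present point does not depend on it.

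**The sections side by side.**
1. {21a}: the DSMC monitors safety and is blinded to assignment.
2. {17a}: patients and clinicians know the arm, and endpoint assessors do not.
3. {21b}: no interim analysis, so no other comparison of arms during the trial is stated.
4. {17b}: no unblinding procedure. The reason given, open-label treatment, fits patients and clinicians but not a committee that {21a} blinds.
5. {22}: adverse events go directly to the DSMC from sites that know the arm. No step for removing the arm from the reports is described. If the arm stays in them, the blinding in {21a} does not hold. If it is removed, the DSMC needs some other way to recover it.

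Two readings of {21a} remain.
- *Pooled data only.* The committee sees one overall rate.
- *Masked arms (A and B).* The committee sees a difference, but the article gives no route to learn which arm is which.

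**What pooling hides.** With 1:1 allocation the pooled rate is (p_control + p_fosinopril) / 2. The rates below are assumptions, because the documents give none. The last column shows what a by-arm comparison could detect with 100 per arm at two-sided 0.05:

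power = Φ{ [|p₁ − p₀| − 1.96 √(2 p̄(1 − p̄)/n)] / √([p₀(1 − p₀) + p₁(1 − p₁)]/n) }

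| Control | Fosinopril | Expected events (control + fosinopril) | Pooled rate | Power by arm |
|---|---|---|---|---|
| 2% | 6% | 2 + 6 | 4% | about 30% |
| 2% | 10% | 2 + 10 | 6% | about 67% |
| 5% | 15% | 5 + 15 | 10% | about 66% |

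For the middle row, the numerator is 0.08 − 1.96 × √(2 × 0.06 × 0.94/100) = 0.08 − 0.0658 = 0.0142. The denominator is √((0.0196 + 0.0900)/100) = 0.0331. Φ(0.43) is about 0.67. In that row, 12 events in 200 patients look the same in pooled form whether they fall 10 to 2 or 6 to 6.

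**Potassium.** It is named in the exclusion criteria and nowhere else. The baseline list names six tests without it, and the follow-up sentence names only NT-ProBNP. Both are introduced as inclusive examples, and the screening tests are not itemised.

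**The case against.** **Blinding need not mean pooled data.** Review by masked arms fits the wording of {21a}, the committee may call for data, and adverse events reach it within a week. This stands. A reader might infer that the DSMC cannot compare harms by arm, but the article does not say so. What remains is that by-arm review is not stated and no unmasking route is given.

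**Table formats and unmasking rules belong in a committee charter.** That is a fair account of the details. The blinding itself is a rule that the article states, however, and not a detail it leaves out. A charter granting access by identified arm would have to depart from that rule.

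**No interim analysis does not forbid safety monitoring.** Agreed. It means only that no other comparison of arms during the trial is stated.

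**By-arm tables would not guarantee detection.** Also agreed: under the assumed rates, power is about 30% to 67% with complete data. That still leaves a chance of seeing an excess, while a pooled rate shows no arm difference at all.

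**Potassium is a missing detail, not a defect.** This largely stands. A reader might infer that potassium is never measured, or that the exclusion cannot be applied. The documents do not support either reading. The lists are open, a renal function panel may contain potassium, laboratory tests are scheduled at screening and every visit, and applying a numerical limit itself requires a measurement. Nor are the other harms that the exclusion criteria anticipate left uncovered. Blood pressure is taken at each follow-up visit ("A brief physical examination will be performed to measure the resting pulse and blood pressure"), renal function is in the baseline list, and angioedema could be picked up by the adverse event questions at each visit.

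**Conclusion.** The point holds for the DSMC. It is blinded to assignment while charged with safety in an open-label trial, with neither by-arm safety review nor a route to unmask stated. On the pooled reading, an arm-specific excess is hidden: an assumed 10% against 2% shows as 6%. On the masked-arm reading, the excess is visible but its direction is not. The percentages are illustrative and rest on assumed rates and 1:1 allocation. The conclusion rests on the stated rules and not on those rates.

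This is an inexpensive improvement to patient safety. It is not evidence that safety monitoring will fail, and it does not affect the primary analysis. The absence of potassium from the named tests is a minor consistency point only.

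**What to change.** Amend {21a}, and reconcile it with {17b} and {22}, to state that:
- the DSMC receives adverse event and safety laboratory tables by arm, at least labelled A and B, and learns the labels on its own request;
- a statistician not involved in running the trial prepares them (the DSMC's planned membership already includes a statistician);
- the tables go to the DSMC only and contain no efficacy comparison;
- individual adverse event reports sent under {22} are handled consistently with this arrangement.

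Separately, reconcile the potassium exclusion criterion with the laboratory tests named in {18a} and Table 1. Clinical thresholds and actions remain with the investigators.

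The cost is some extra tabulation of data already collected, and care in keeping the by-arm tables within the committee. Without an efficacy look there is no alpha cost and no change to the sample size.
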